#### Qualitative analyses

The audiotapes of all interviews will be transcribed verbatim. This data will be analyzed by two independent researchers with ATLAS.ti 7 software according to the thick analysis approach [92]. This approach endorses multiple triangulations, i.e., the use of multiple interpreters and techniques to analyze the data, to enhance validity.

The coding and analyses will be an iterative process simultaneously with the interviews, allowing adjustment of questions and topics. We will make use of open coding, thematic coding, and causal coding [93]. Open coding is an explorative process in which all elements of the data are coded. Thematic coding is a more deductive technique that included the coding of themes and categories that are proposed by the researchers prior to the analysis or emerge from the material and are considered to be of importance by the researchers. Causal coding will help us to get more insight into the working elements of the DICE approach as proposed by the participants. Characteristics of patients and their caregivers (age, sex, relationship, disease severity) will be used for descriptive purposes.

## Discussion

The current paper describes the protocol of the BEAT-IT study, a multicenter study designed to investigate the effectiveness of a comprehensive assessment and personalized treatment of NPS in AD, following the DICE method to improve the QoL in patients with MCI and AD in the memory clinic. We hypothesize that early recognition and tailored treatment of NPS will benefit the QoL of patients and their caregivers; will reduce NPS, caregiver burden, and psychotropic drug use; and will lead to cost-effective care.

The novelty of this study lies in the inclusion of the whole spectrum of NPS, the enrollment of both patients with MCI and AD, and the evaluation of an approach that integrates both nonpharmacological and pharmacological interventions in the memory clinic setting. Besides standardized quantitative measures, a qualitative approach will be used to examine its efficacy and feasibility from the perspective of caregivers and patients. Also, important additional information will be obtained from studying the first wave of participants, enabling us to examine “naturalistic” progression of NPS and its relationship with other clinical measures. Insight in the current CAU of NPS will aid us in the formulation of recommendations to improve the daily clinical practice regarding the care of NPS in AD. After establishing the effectivity of the DICE method in the memory clinic setting, a next step would be to examine the implementation of this approach at other sites by taking already suggested and unique local barriers into account.

At the time of writing, recruitment is ongoing and is expected to be completed in December 2019 for the control group. Hereafter, the intervention group will be enrolled until the beginning of 2021, and follow-up measures will be completed in autumn 2021. Results will be available in late 2021.

There are a few possible threats to this study. Firstly, the use of the NPI-Q to screen for eligible patients might introduce an observer bias since this measure is not part of the regular diagnostic workup at some sites. Consequently, NPS may be detected more often, resulting in care that may not fully reflect the current CAU, i.e., underestimating the expected underrecognition and undertreatment of NPS in AD. Second, the current guidelines consider psychosocial interventions as the first-line treatment but mainly suggest interventions that may be more suitable for institutionalized patients with severe dementia, e.g., reminiscence therapy, aromatherapy, or “snoezelen” [24, 25]. Although various nonpharmacological interventions have been shown to be effective in community-dwelling patients [18], these strategies are rarely mentioned in the guidelines and therefore not integrated in clinical practice [94]. For our interventions, we will select nonpharmacological strategies based on prior studies (e.g., [48]) and our clinical expertise. Third, our outcome measures are mainly based on self-reported questionnaires that may not fully capture all effective aspects of the intervention [95, 96]. Moreover, patients with dementia may have difficulties completing the QoL questionnaires (EQ-5D-5 L, ICECAP-O) due to cognitive problems [97]. To circumvent some of these problems, we will also use qualitative research methods which enables us to better understand and measure the QoL of patients and to give participants the opportunity to express their experiences with the DICE method in an unrestricted manner. Fourth, the substantial differences across sites in CAU might be a challenge to this study, as patients visiting certain sites may receive more and different treatments compared to other centers. We will therefore aim to record all valuable information through our CRF, which enables us to perform post hoc sensitivity analyses, and verify whether this heterogeneity might affect the results. A final issue might be that patients are included based on clinical diagnostic criteria, without the use of AD pathophysiological biomarkers (e.g., abnormal levels of Aβ or tau proteins in CSF or on PET). Despite the fact that an MRI or (FDG-)PET scan of the brain is required, this may lead to the inclusion of patients who do not have underlying AD pathology, especially in those with MCI. However, the applied diagnostic criteria resemble those that are used in clinical practice where AD pathophysiological biomarkers are not part of the standard diagnostic workup. In addition, since this is a clinical study targeting clinical symptoms rather than the underlying disease process, we argue that the effects might be similar in patients with other underlying etiologies. We will however perform a sensitivity analysis in a subgroup of patients with positive AD biomarkers in order to study whether the effects are similar in this subgroup compared to the whole study group.

To conclude, the BEAT-IT study as a whole will increase our knowledge of the underlying neurobiology of NPS in AD, which may enable us to identify potential targets for therapeutic agents. The intervention study might provide evidence on how to structure and standardize the care of NPS in AD to improve the QoL of both caregivers and patients. Moreover, the findings of the intervention study will result in recommendations to improve the early detection and treatment of NPS in AD in the memory clinic.

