### Outcome measures

For the control group, measurements will take place at baseline (T0), with follow-up testing at 3 months (T1) and 6 months (T2). For the intervention group, measurements will take place at baseline (T0), directly after treatment (T1), and follow-up at 6 months (T2). The T1 measurements will be planned after finishing the (psychosocial) intervention and/or when medication is stabilized and thus may vary between subjects in the intervention group. We will gather all relevant clinical and intervention-related information which enables us to study post hoc whether this variation in T1 assessments may have resulted in bias. All measurements will take place at the local hospitals or at the patients’ homes, see Table 2 for an overview of all outcome measures.

**Table 2 Tab2:** Outcome measures

Outcome	Measure	Purpose	Respondent	Time of assessment
Demographic characteristics	For example, age, education, sex, ethnicity, relation to caregiver	Descriptive, covariate, moderator	Patient and caregiver	T0
Clinical characteristics	For example, diagnosis, AD biomarkers, disease duration	Descriptive, moderator	Patient and caregiver	T0*
Disease severity	CDR [57]	Descriptive, moderator	Patient	T0*, T2
Cognitive status	MMSE [58]	Descriptive, moderator	Patient	T0*, T2
Cognitive functioning	Standardized cognitive test battery [43]: RAVLT [59], VAT [60], DS [61], VF [62], LDST [63], SCWT [64], TMT [65]	Descriptive, moderator	Patient	T0*
Functional abilities	A-IADL-Q [66]	Descriptive, moderator	Caregiver	T0, T2
Psychotropic medications	Brown bag review [20]	Descriptive, secondary outcome	Caregiver	T0, T1, T2
Comorbidities	CIRS-G [50]	Descriptive	Patient	T0, T2
Quality of life patient	QoL-AD [67]	Primary outcome	Patient and caregiver	T0, T1, T2
Quality of life caregiver	CarerQol-7D [53]	Primary outcome	Caregiver	T0, T1, T2
Caregiver burden	Perseverance time [68]	Secondary outcome	Caregiver	T0, T1, T2
Caregiver competence managing NPS	Additional NPI-Q item [69]	Secondary outcome	Caregiver	T0, T1, T2
Cost-effectiveness	EQ-5D-5 L [70], ICECAP-O [71] iMTA iVICQ [72], iMTA MCQ [73]	Secondary outcome	Patient Caregiver	T0, T1, T2
NPS prevalence, severity, and distress	NPI-Q [44]	Secondary outcome	Caregiver	T0*, T1, T2
If NPI-Q frequency score ≥ 1 on:				
“Agitation,” “motor disturbances,” “irritability,” “disinhibition”	Cohen-Mansfield Agitation Inventory [74]	Secondary outcome	Caregiver	T0, T1, T2

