“Apathy”	Apathy Evaluation Scale-I [75]	Secondary outcome	Caregiver	T0, T1, T2
“Depression,” “anxiety,” “elation”	CSDD [76], RAID [77]	Secondary outcome	Caregiver	T0, T1, T2
“Hallucinations,” “delusions”	BEHAVE-AD subscales psychosis, delusions [78]	Secondary outcome	Caregiver	T0, T1, T2
“Nighttime behaviors”	Sleep Disorder Inventory [79]	Secondary outcome	Caregiver	T0, T1, T2

*AD* Alzheimer’s disease, *CDR* Clinical Dementia Rating, *RAVLT* Rey Auditory Verbal Learning Test, *VAT* Visual Association Test, *DS* Digit Span, *VF* Verbal Fluency (animals), *LDST* Letter Digit Substitution Test, *SCWT* Stroop Color Word Test, *TMT* Trail Making Test, *MMSE* Mini-Mental State Examination, *A-IADL-Q* Amsterdam Instrumental Activity of Daily Living Questionnaire, *CIRS-G* Cumulative Illness Rating Scale for Geriatrics, *QoL-AD* Quality of Life in Alzheimer’s Disease, *iMTA iVIQ* iMTA Valuation of Informal Care Questionnaire, *iMTA MCQ* iMTA Medical Costs Questionnaire, *NPI-Q* Neuropsychiatric Inventory Questionnaire, *CSDD* Cornell Scale for Depression in Dementia, *RAID* Rating Anxiety In Dementia, *BEHAVE-AD* Behavioral Pathology in Alzheimer’s Disease Rating Scale

*Will be carried out during the diagnostic procedure at local hospitals

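### The biomarker sensitivity analysis compares biomarker-positive patients with a whole group that contains them, which shrinks any real difference and gives no estimate in biomarker-negative patients

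*Protocol article*

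**What the plan says.** The protocol article's Discussion lists as a limitation that "patients are included based on clinical diagnostic criteria, without the use of AD pathophysiological biomarkers" and adds that "this may lead to the inclusion of patients who do not have underlying AD pathology, especially in those with MCI". It defends this in two ways. The criteria match practice, where "AD pathophysiological biomarkers are not part of the standard diagnostic workup". And because the study targets symptoms rather than the disease process, "we argue that the effects might be similar in patients with other underlying etiologies". The next sentence offers a sensitivity analysis restricted to biomarker-positive patients, to study "whether the effects are similar in this subgroup compared to the whole study group".

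Table 2 (Outcome measures) records biomarkers in the clinical characteristics row, "For example, diagnosis, AD biomarkers, disease duration". The purpose column marks that row as descriptive and as a moderator. Its time point is T0 with an asterisk, and the footnote reads "Will be carried out during the diagnostic procedure at local hospitals". The Statistical methods section describes no analysis by biomarker status. The document gives no share tested, no share positive and no criterion for calling effects similar.

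**The concern.** The argument just before the analysis is about patients whose symptoms have another cause. The stated comparison does not estimate an effect in them. It sets positives against a total made up of those same positives, the known negatives and any untested patients, some of whom may also have AD pathology. The two estimates share patients, so part of their agreement comes from the overlap.

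There is a second issue. Biomarkers come from local work-up and are not routine, so a positive patient may also be one who was chosen for testing. The article does not describe who is tested. If testing follows site or presentation, the subgroup differs from the whole in more than AD pathology, and the bias could go either way.

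At stake is the interpretation of one secondary analysis. A finding of similar effects could be reported as reassurance about patients without AD pathology, which it would barely support.

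**Working it through.** **Inputs from the document.** N = 150, 75 per wave; alpha 0.05; power 0.80; a moderate effect with no number; required N of 86 for the between-group analysis (Sample size). No figure is given for the biomarker analysis.

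**Assumptions.** p, the share with AD pathology, 0.5 to 0.9. True effects of 0.5 SD in positives (d+) and 0 in negatives (d-). Share tested 30%, 50% or 100%, at random. 1:1 allocation, no dropout, and no precision gained from baseline or repeated measures.

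**The plan's own figure.** A between-factor repeated-measures ANOVA with f = 0.25 (d = 0.5), two groups, three measurements, correlation 0.5, alpha 0.05 and power 0.80 gives N = 86, as stated. The article does not print f, the number of measurements or the correlation. The match makes 0.5 SD a fair reading of moderate. The within-group figure of 46 does not follow from the same inputs (they give 28), but nothing here depends on it.

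**Size of the contrast.**
- Whole-group effect = p × d+ + (1 - p) × d-.
- Positive minus whole = d+ - [p × d+ + (1 - p) × d-] = (1 - p) × (d+ - d-).
- With d+ - d- = 0.5: 0.50 × 0.5 = 0.25 at p = 0.5; 0.30 × 0.5 = 0.15 at p = 0.7; 0.20 × 0.5 = 0.10 at p = 0.8; 0.10 × 0.5 = 0.05 at p = 0.9.
- Positive minus negative is 0.50 at every p.

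Here p is the true share with pathology, not the share known to be positive, so testing few patients at random does not reduce the dilution.

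**Precision.** In SD units each effect has variance 4/n.
- Positive minus whole, overlap respected: 4/n+ - 4/150.
- Positive minus negative: 4/n+ + 4/n-.

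Example with 50% tested and p = 0.7: n+ = 52.5, n- = 22.5.
- Planned contrast: SE = √(0.0762 - 0.0267) = 0.22 for a gap of 0.15; power 10%.
- Direct contrast: SE = √(0.0762 + 0.1778) = 0.50 for a gap of 0.50; power 17%. The 95% CI half-width is 1.96 × 0.504 = 0.99 SD.

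Power, planned contrast / direct contrast:

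| p | Planned gap (SD) | All 150 tested | 50% tested | 30% tested |
|---|---|---|---|---|
| 0.5 | 0.25 | 33% / 33% | 14% / 19% | 10% / 13% |
| 0.7 | 0.15 | 29% / 29% | 10% / 17% | 8% / 12% |
| 0.8 | 0.10 | 23% / 23% | 8% / 14% | 6% / 10% |
| 0.9 | 0.05 | 15% / 15% | 6% / 10% | 5% / 8% |

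With everyone tested the two tests are equivalent. The planned variance becomes 4(1 - p)/(150p) and the direct variance 4/(150p(1 - p)), so both give the same z. That needs the overlap to be modelled. If the two estimates are treated as independent, z at p = 0.7 falls from 1.40 to 0.59.

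**The case against.** The best defence is that the analysis has a narrower and legitimate purpose: to show whether the result holds in biomarker-confirmed AD. Any restricted-population sensitivity analysis overlaps with the full sample, as this protocol's per-protocol and intention-to-treat analyses do. The authors only argue that effects might be similar in other etiologies, and they give a clinical reason. Eligibility already requires at least intermediate probability of AD etiology and excludes other neurodegenerative disease. Table 2 names the biomarker row as a moderator, so a moderator analysis may be intended and detailed in an analysis plan that is not shown. The alternative is also weak: its larger contrast carries a larger standard error, its power is at most 33%, and it is open to the same selection for testing.

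Most of this stands. It limits the point to a secondary analysis, and it is why the biomarker-positive analysis should stay. It does not justify the stated comparator as a test of similarity. Strict eligibility would raise p and so increase the dilution. The moderator label supports a direct contrast, while the only comparison described is part against whole.

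A reader might infer three stronger things that the document does not support:
- That the whole group is mostly positive. No share is given. If, say, 30% were tested and 80% of those were positive, known positives would be 24% of the sample.
- That only clinically selected patients are tested. Local, non-routine work-up makes selection plausible, but testing practice is not described.
- That the check is bound to show similar effects. The difference is attenuated, not removed, and selection for testing could create a spurious one.

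**Conclusion.** The point holds as one of attenuation and of a missing estimate. Under random testing the planned comparison shows only (1 - p) of the true positive-versus-negative difference: 50% at p = 0.5 down to 10% at p = 0.9, with p assumed. It gives no effect in biomarker-negative patients, so a similar result would be weak evidence on other etiologies. With 30% to 50% tested, the chance of detecting even a complete loss of a 0.5 SD effect is about 5% to 14%.

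The direct contrast improves detection only modestly, to 8% to 19% in the same range. Its real gain is that it targets the right quantity and shows the uncertainty in its interval. The power figures rest on the assumed effects, shares and simple variances above and are indicative. Neither the primary result nor the trial's conduct is affected.

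**What to change.** 1. Keep the biomarker-positive analysis, described only as a check that the result holds in biomarker-confirmed AD.
2. For the similarity question, and in line with the moderator label in Table 2, estimate the DICE-versus-CAU effect separately in biomarker-positive and biomarker-negative patients, with untested patients reported separately. Give the group-by-biomarker interaction with its 95% CI, with hospital in the model.
3. Report the number tested and the percentage positive by wave and hospital. The two groups are successive waves, so a shift in testing between them would otherwise go unseen.
4. State that similarity will not be concluded from a wide interval.

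The cost is analysis wording; biomarker results are already recorded and no new tests are needed. The drawback is that the negative group may be small and the interval wide, so the answer may be that the data cannot tell. The interaction should be read as an estimate only. It does not remove bias from selection for testing, but the counts in item 3 let readers judge it.

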## Abbreviations

AD: Alzheimer’s disease
AES-I: Apathy Evaluation Scale Information version
A-IADL-Q: Amsterdam Instrumental Activities of Daily Living Questionnaire
BEHAVE-AD: Behavioral Pathology in Alzheimer’s Disease Rating Scale
bvAD: Behavioral variant of AD
CAU: Care as usual
CDR: Clinical Dementia Rating Scale
CIRS-G: Cumulative Illness Rating Scale for Geriatrics
CMAI-D: Dutch version of Cohen-Mansfield Agitation Inventory
CRF: Care report form
CSDD: Cornell Scale for Depression in Dementia
CSF: Cerebrospinal fluid
FDG-PET: Fluorodeoxyglucose positron-emission tomography
IADL: Instrumental activity of daily living
ICECAP-O: ICEpop CAPability measure for Older people
iMTA iVICQ: Institute for Medical Technology Assessment Valuation of Informal Care Questionnaire
iMTA MCQ: Institute for Medical Technology Assessment Medical Consumption Questionnaire
MCI: Mild cognitive impairment
MMSE: Mini-Mental State Examination
MRI: Magnetic resonance imaging
NPI-Q: Neuropsychiatric Inventory Questionnaire
NPS: Neuropsychiatric symptoms
PCC: Patient-centered care
PET: Positron-emission tomography
QALY: Quality-adjusted life years
QoL: Quality of life
QoL-AD: Quality of Life in Alzheimer’s Disease questionnaire
RAID: Rating Anxiety in Dementia
SDI: Sleep Disorder Inventory
